### Primary objective

Assess the standard diagnostic accuracy of POCTs for active SARS-CoV-2 infection compared to the Public Health England (PHE) reference laboratory standard or equivalent

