### Composite reference standards

An assumption of standard diagnostic accuracy studies is that the reference standard is infallible. This constrains the performance of the index test to the performance of the reference standard and assumes every time the tests get different results the reference is correct and the index is incorrect. There is evidence of substantial heterogeneity of diagnostic accuracy of SARS-CoV-2 d/rRT-PCR testing, with reported false negative rates of 18–58% [36]. Both clinical context and repeated testing are highly relevant to calculating the likelihood of true negative cases [37], and so we will undertake further analyses using the composite reference standard.

Composite reference standard 1 will be designed to minimise false negatives (FNs), and composite reference standard 2 will be designed minimise false positives (FPs). Both composite reference standards will be constructed considering paired antibody test results, patient reported outcomes, linked EHRs for outcomes related to COVID-19, such as hospitalisation or death, other test results (Table 4).

**Table 4 Tab4:** Potential use of tests to enhance the reference standard. Information in the table refers to hypothetical combinations of results in which the enhanced reference standard result would be considered different from the original reference standard result. A cell-by-cell interpretation of each scenario follows.

	Minimise FN for current infection		Minimise FN for past infection	
Visit (day)	1 (0)	2 (28)	1 (0)	2 (28)
**SARS-CoV-2 RT-PCR**	Negative (FN)	N/A	Negative	N/A
**COVID IgG**	Negative	Positive	Negative (FN)	Positive
Or:	Subsequent positive SARS-Cov-2 RT-PCR result (within 28 days)		-	
Or:	Hospital admission or death (within 28 days) citing SARS-CoV-2 as probable cause		Hospital admission or death (within 28 days) citing SARS-CoV-2 as probable cause	
	**Minimise FP for current infection**		**Minimise FP for past infection**	
**Visit (day)**	1 (day 0)	2 (28)	1 (day 0)	2 (28)
**SARS-CoV-2 RT-PCR**	Positive (FP)	N/A	Negative	N/A
1.1.35. **COVID IgG**	Negative	Negative	Positive (FP)	Negative
And:	No subsequent positive SARS-Cov-2 RT-PCR result (within 28 days)		-	
And:	No hospital admission or death (within 28 days) citing SARS-CoV-2 as probable cause		No hospital admission or death (within 28 days) citing SARS-CoV-2 as probable cause	

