### Summary statistics of diagnostic accuracy

Sensitivity, specificity, and positive and negative predictive values for each POCT will be calculated with exact 95% confidence intervals.

For the primary outcome and first secondary outcome:

For consecutive POCTs for active infection, the diagnostic accuracy of each POCT will be summarised independently using 2 × 2 tables for POCT (+/-) and the current standard PHE reference test (+/-) for active infection. For consecutive POCTs for past infection, the diagnostic accuracy of each POCT will be summarised independently using 2 × 2 tables for POCT (+/-) and the current standard PHE reference test (+/-) for past infection. Measures of diagnostic accuracy will also be presented adjusted for imperfect reference standard bias, using the best available estimate of the accuracy of the PHE reference test.

For the second and third secondary outcomes:

For consecutive POCTs for active infection, the enhanced diagnostic accuracy of each POCT will be summarised independently using 2 × 2 tables for POCT (+/-) and the composite reference standards as outlined in Table 4 (+/-). For consecutive POCTs for past infection, the enhanced diagnostic accuracy of each POCT will be summarised independently using 2 × 2 tables for POCT (+/-) and the composite reference standards (+/-) for past infection.

Results for the primary outcome will be stratified by adults vs children, by age group (< 16, 16–40, 40–60, 60+ years), by gender, by ethnicity and by spectrum of disease (a combined measure of symptom severity and duration). A further subgroup analysis will test for differences in diagnostic performance by practice, and if any differences are detected, associations with practice size, location and model of care will be explored.

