### Number of participants

We have calculated sample sizes using standard methodology based on minimum clinically relevant sensitivity or specificity (whichever is the most critical for the intended placement in the care pathway), not expected values from preliminary work [16]. For example, acceptable thresholds for minimum sensitivity and specificity of 80% and 95% respectively, can be used to determine sample size requirements and a strategy for early identification of poorly performing tests.

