### Stopping criteria

Assuming a test with 90% sensitivity, a 99% specificity, and a pre-test probability (prevalence) of 30%, we would require 200 participants to meet the minimum thresholds as stated above. This would also mean that tests with more than seven false negatives or two false positives could be immediately dropped from the study. This allows us to exclude tests with sensitivities of 50%, 60%, 70%, or 80% after the first 50, 60, 80, and 120 participants recruited. For tests with poor specificities of 80%, 85%, 90%, or 95% these would be identified after 15, 20, 30, and 60 participants recruited. The prevalence of COVID-19 affects the sample size required. With a pre-test probability (prevalence) of 5% we would require 1200 participants to evaluate a POCT and interim futility analyses will stop the evaluation after seven false negatives or twelve false positives. POCTs with an actual sensitivity of 50%, 60%, 70%, or 80% would reach futility criteria after the first 280, 350, 470, and 700 participants. POCTs with an actual specificity of 80%, 85%, 90% or 95% would reach futility criteria after the first 65, 85, 130, and 255 recruited participants.

Evaluations of the first POCTs will be performed without implementation of stopping criteria to establish whether sufficient information to create the composite reference standard can be obtained sufficiently quickly to make these criteria viable. The figures presented here should therefore be regarded as indicative for a POCT designed to detect active infection and will be reviewed once this information becomes available.

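### Adjusting POCT accuracy with one best estimate of RT-PCR accuracy is fragile, given the protocol's own 18–58% range of RT-PCR false-negative rates

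*Protocol article*

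**What the plan says.** The primary objective (Protocol article, Primary objective) is: "Assess the standard diagnostic accuracy of POCTs for active SARS-CoV-2 infection compared to the Public Health England (PHE) reference laboratory standard or equivalent". Under Summary statistics of diagnostic accuracy, each POCT is summarised in a 2 × 2 table against the current PHE reference test, and "Sensitivity, specificity, and positive and negative predictive values for each POCT will be calculated with exact 95% confidence intervals". For the primary and first secondary outcomes the section then adds: "Measures of diagnostic accuracy will also be presented adjusted for imperfect reference standard bias, using the best available estimate of the accuracy of the PHE" (that is, of the PHE laboratory test). It gives no correction method and no value for that estimate.

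Under Composite reference standards, the article describes RT-PCR accuracy as substantially heterogeneous, "with reported false negative rates of 18–58" per cent.

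Three planning statements supply the figures used below:
- Number of participants gives, as an example, "acceptable thresholds for minimum sensitivity and specificity of 80% and 95% respectively".
- Stopping criteria: "Assuming a test with 90% sensitivity, a 99% specificity, and a pre-test probability (prevalence) of 30%, we would require 200 participants" to meet those minimum values.
- Stopping criteria, low prevalence: "With a pre-test probability (prevalence) of 5% we would require 1200 participants".

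**The concern.** A 2 × 2 table against an imperfect reference does not by itself identify the true accuracy of the index test. A correction needs a value for the reference's sensitivity and specificity, and an assumption about whether the two tests err together. The wording points to one value, while another section of the same article allows RT-PCR sensitivity anywhere from 42% to 82% (100% minus 58% and 18%).

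Independent errors are also doubtful here. Index tests for active infection may use an OP/NP swab or saliva taken at the same visit as the reference swab, so a low viral load can make both tests miss the same patient.

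At stake is what the adjusted results can support. An adjusted specificity may fall outside 0–100%. It may also sit on the other side of a minimum value from the unadjusted result, with no statement of which one counts.

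**Working it through.** **The plan's own arithmetic.** The article states no adjusted figure to reproduce. Its sizing figures do reproduce. Table 5 at 90% sensitivity, 30% prevalence and a standard error of 2.5% gives 0.90 × 0.10 / 0.025² / 0.30 = 480, as stated. The run lengths in Stopping criteria follow from simple counts. For 50% sensitivity, 7 / (0.30 × 0.50) = 47, stated as 50. For 80% specificity, 2 / (0.70 × 0.20) = 14, stated as 15.

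**Assumed correction.** Let a, b, c, d be the POCT+/PCR+, POCT+/PCR−, POCT−/PCR+ and POCT−/PCR− cells, N their total and SeR the RT-PCR sensitivity. The usual closed form under conditional independence is

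Sp = [(c+d)·SeR − c] / [N·SeR − (a+c)].

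It exceeds 1 when SeR is below a/(a+b) (for SeR above the observed proportion PCR-positive), and it does not depend on RT-PCR specificity.

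**Reading A: 90%/99% are accuracy against RT-PCR.**

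At 30% positive and N=200, the cells are a=54, b=1.4, c=6, d=138.6.
- SeR 82%: (144.6 × 0.82 − 6) / (164 − 60) = 112.572 / 104 = 108.2%.
- SeR 42%: (144.6 × 0.42 − 6) / (84 − 60) = 54.732 / 24 = 228.1%.
- Above 100% for any SeR below 54 / 55.4 = 97.5%.

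At 5% positive and N=1200, the cells are a=54, b=11.4, c=6, d=1128.6.
- SeR 82%: (1134.6 × 0.82 − 6) / (984 − 60) = 924.372 / 924 = 100.04%.
- SeR 42%: (1134.6 × 0.42 − 6) / (504 − 60) = 470.532 / 444 = 106.0%.

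**Reading B: 90%/99% are true values, errors are independent, and RT-PCR specificity is 100% (assumed; the article gives none).**

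Unadjusted specificity is the share of RT-PCR negatives that are POCT negative. At 30% prevalence:
- SeR 82%: (0.30 × 0.10 × 0.18 + 0.70 × 0.99) / (0.30 × 0.18 + 0.70) = 0.6984 / 0.754 = 92.6%.
- SeR 42%: (0.30 × 0.10 × 0.58 + 0.70 × 0.99) / (0.30 × 0.58 + 0.70) = 0.7104 / 0.874 = 81.3%.

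With the correct SeR plugged in, the correction returns 99% in expectation. One POCT would therefore be below 95% unadjusted and above it adjusted. At 5% prevalence the unadjusted values are 98.2% and 96.4%, both above 95%, so that conflict does not arise.

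**Dependence on the plug-in.** Keep reading B at 30% prevalence with a true SeR of 82%. The expected cell proportions are c = 0.0246, c+d = 0.723 and a+c = 0.246.
- Plug in 95%: (0.723 × 0.95 − 0.0246) / (0.95 − 0.246) = 94.1%.
- Plug in 82%: (0.723 × 0.82 − 0.0246) / (0.82 − 0.246) = 99.0%.
- Plug in 70%: (0.723 × 0.70 − 0.0246) / (0.70 − 0.246) = 106.1%.

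In 20,000 simulated studies of N=200 under the same conditions, adjusted specificity exceeded 100% in 36% of samples with the correct plug-in of 82%, and in 96% with a plug-in of 70%.

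**The case against.** The strongest reply has four parts.

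- **Ranking.** A reader might infer that the two versions stand unranked. The documents do not support that. The primary objective is standard accuracy against the PHE laboratory reference, Table 3 uses no composite for that question, and the adjusted measures are presented in addition. This part of the reply stands; only an explicit statement is missing.
- **Impossible values.** A reader might infer that the adjusted specificity is bound to exceed 100%. That is not supported either. The article names no formula. Prevalence in Stopping criteria can be read as true prevalence, in which case the expected adjusted value is 99%. The 18–58% range describes RT-PCR testing generally, and the PHE assay's own accuracy may lie elsewhere. The excess at 5% prevalence and an 18% false-negative rate is 0.04 points. All of this stands as a limit on the size of the point.
- **Thresholds.** The 80%/95% values are introduced as an example for sizing and early identification of poor tests. The stopping figures are called indicative and are not applied to the first POCTs. Nowhere is an adjusted estimate compared with them. This also stands: the conflict shown is a possibility, not a planned decision rule.
- **SAP.** Method, error dependence and interval construction are normally SAP content, and the article defers details to a SAP that is not shown. Their absence is therefore no fault here. What can be criticised is the wording that ties the adjustment to one estimate. The composite reference standards address reference error in a separate analysis and do not change that wording.

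**Conclusion.** The point holds in limited form. The article bases its adjusted accuracy on one best estimate of the reference test's accuracy while reporting a range of RT-PCR false-negative rates so wide that the choice of value largely determines the result.

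At 30% prevalence the consequence is large under either reading. Under reading A, adjusted specificity is 108% to 228%. Under reading B, unadjusted specificity is 92.6% to 81.3% against an expected adjusted 99%. At 5% prevalence it is small: 100.04% to 106% under reading A, and no crossing of 95% under reading B.

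These sizes rest on the conditional-independence correction, on the 18–58% range applying to the reference in use and, for reading B, on RT-PCR specificity of 100%. They concern active infection only, since the article gives no comparable range for the antibody reference. The primary unadjusted analysis is not affected. The issue is what the adjusted figures can support and how they are labelled.

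**What to change.** In Summary statistics of diagnostic accuracy:

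1. State that the unadjusted comparison with the PHE reference is the result judged against the minimum sensitivity and specificity.
2. Label the adjusted figures for active infection a sensitivity analysis, and present them over a range of RT-PCR accuracy that covers false-negative rates of 18–58% in place of one estimate.
3. Use a method that allows POCT and RT-PCR errors to be correlated, keeps estimates within 0–100%, and carries the uncertainty in RT-PCR accuracy into the intervals. A Bayesian latent-class model with a dependence term and a prior on RT-PCR accuracy is one option.

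The cost is a few sentences in the protocol or SAP and a modest amount of analysis code, with no extra data. The drawback is that adjusted accuracy becomes a range, often a wide one, where a single figure was promised.

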### Missing data

Missing data for test results including reference tests will be reported. Potential associations between patient characteristics (e.g. age, gender) and the pattern of missing data will be evaluated and reported using tables and graphs. Robustness of the estimates for accuracy will be evaluated using sensitivity analyses.

### Number of participants

We have calculated sample sizes using standard methodology based on minimum clinically relevant sensitivity or specificity (whichever is the most critical for the intended placement in the care pathway), not expected values from preliminary work [16]. For example, acceptable thresholds for minimum sensitivity and specificity of 80% and 95% respectively, can be used to determine sample size requirements and a strategy for early identification of poorly performing tests.

### Stopping criteria

Assuming a test with 90% sensitivity, a 99% specificity, and a pre-test probability (prevalence) of 30%, we would require 200 participants to meet the minimum thresholds as stated above. This would also mean that tests with more than seven false negatives or two false positives could be immediately dropped from the study. This allows us to exclude tests with sensitivities of 50%, 60%, 70%, or 80% after the first 50, 60, 80, and 120 participants recruited. For tests with poor specificities of 80%, 85%, 90%, or 95% these would be identified after 15, 20, 30, and 60 participants recruited. The prevalence of COVID-19 affects the sample size required. With a pre-test probability (prevalence) of 5% we would require 1200 participants to evaluate a POCT and interim futility analyses will stop the evaluation after seven false negatives or twelve false positives. POCTs with an actual sensitivity of 50%, 60%, 70%, or 80% would reach futility criteria after the first 280, 350, 470, and 700 participants. POCTs with an actual specificity of 80%, 85%, 90% or 95% would reach futility criteria after the first 65, 85, 130, and 255 recruited participants.

Evaluations of the first POCTs will be performed without implementation of stopping criteria to establish whether sufficient information to create the composite reference standard can be obtained sufficiently quickly to make these criteria viable. The figures presented here should therefore be regarded as indicative for a POCT designed to detect active infection and will be reviewed once this information becomes available.

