A strength of the RAPTOR-C19 protocol is the stopping criteria to identify POCTs that have already exceeded the maximum number of false positives or false negatives necessary to be able achieve the target sensitivity and specificity. A corresponding weakness is that a test which has focussed on achieving high sensitivity but has low specificity may be disadvantaged in a low prevalence setting, especially if the anticipated prevalence used to set the stopping criteria, was higher than the actual prevalence. In this circumstance, tests may be excluded from the analysis because of accumulating too many false positive results in comparison to the laboratory and composite reference standards. Nevertheless, these stopping criteria reflect MHRA mandated performance criteria. During early evaluations we will establish whether sufficient information to create the composite reference standard can be obtained sufficiently quickly to make stopping criteria viable.

We recognise the challenges of recruitment in a changing policy environment, with variable disease prevalence. GP sites will be recruited from the RCGP Research and Surveillance Centre (RSC) is an internationally renowned source of information, analysis, and interpretation of primary care data [40]. The dataset is nationally representative [41], having only small differences with the national population, which have now been quantified and can be assessed for clinical relevance for specific studies. With twice weekly data extractions, the dataset is one of the most up to date in the UK, and now a platform within ORCHID. ORCHID is in the process of enhancing the frequency of extraction and scope of data linkage. It is already extracting primary care computerised medical records (CMRs) daily and linking with linked hospital data and mortality data. ORCHID will additionally support RAPTOR-C19 by allowing patient follow-up within the RCGP RSC network, and the creation of an enhanced composite reference standard to overcome limitations of laboratory reference tests [30].

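### The seven-false-negative and two-false-positive limits are not the maximum counts compatible with 80% sensitivity and 95% specificity: a test with the assumed 90%/99% accuracy crosses them about 37% of the time, or 64% if dropped on reaching them

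*Protocol article*

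**What the plan says.** Under Number of participants, the protocol article gives as its example "acceptable thresholds for minimum sensitivity and specificity of 80% and 95% respectively".

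Under Stopping criteria it sets the first scenario, "Assuming a test with 90% sensitivity, a 99% specificity, and a pre-test probability (prevalence) of 30"%, and concludes that "we would require 200 participants to meet the minimum thresholds as stated above". It then says that "tests with more than seven false negatives or two false positives could be immediately dropped from the study". In the second scenario, with 5% prevalence and 1200 participants, "interim futility analyses will stop the evaluation after seven false negatives or twelve false positives". Both scenarios come with the numbers of participants after which poor tests would be excluded. The first evaluations are to run without stopping criteria, and "The figures presented here should therefore be regarded as indicative for a POCT designed to detect active infection".

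Under Strengths and limitations, the rules are described as identifying tests that have already "exceeded the maximum number of false positives or false negatives necessary to be able achieve the target sensitivity and specificity".

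Under Summary statistics of diagnostic accuracy, sensitivity and specificity "will be calculated with exact 95% confidence intervals". The article gives no level, sidedness, power or definition of meeting a threshold for the figure of 200.

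**The concern.** A limit that marks the largest error count still compatible with 80% sensitivity or 95% specificity should follow from those thresholds, the number of reference-positives or reference-negatives, and the chosen interval. The stated limits instead lie just above the error counts expected from a good test. A test that performs exactly as assumed would then often be dropped by chance, while the text suggests that only tests unable to reach the minimum standard are dropped. The platform exists to pick out good tests, so the chance of wrongly dropping one is a main operating characteristic of the rule, and the article does not give it.

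The wording also shifts. For the same 60 expected cases, a test must exceed seven false negatives in one scenario but is stopped after seven in the other.

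**Working it through.** **Inputs** (Number of participants; Stopping criteria; Summary statistics of diagnostic accuracy). Assumed accuracy 90%/99%; thresholds 80%/95%; exact 95% intervals, taken as two-sided.
- 30% prevalence, 200 participants: 60 reference-positives, 140 reference-negatives. Expected errors: 60 × 0.10 = 6 false negatives (FN) and 140 × 0.01 = 1.4 false positives (FP). Limits: 7 and 2.
- 5% prevalence, 1200 participants: 60 and 1140. Expected errors: 6 FN and 11.4 FP. Limits: 7 and 12.

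**1. Reproducing the plan's figures.**

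*Sample size.* The score formula at two-sided 5% and 50% power gives 1.96² × 0.8 × 0.2 / (0.9 − 0.8)² = 61.5 positives. That is 61.5/0.30 = 205 and 61.5/0.05 = 1229 participants, close to 200 and 1200. The same formula at 80% power gives 107.4 positives, about 358 participants at 30% prevalence.

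*Participants until a poor test is excluded.* The expected number is limit / (prevalence × (1 − sensitivity)), or limit / ((1 − prevalence) × (1 − specificity)).

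| Scenario | Stated | On reaching the limit | On exceeding it |
|---|---|---|---|
| 30%, FN (sensitivity 50, 60, 70, 80%) | 50, 60, 80, 120 | 47, 58, 78, 117 | 53, 67, 89, 133 |
| 30%, FP (specificity 80, 85, 90, 95%) | 15, 20, 30, 60 | 14, 19, 29, 57 | 21, 29, 43, 86 |
| 5%, FN | 280, 350, 470, 700 | 280, 350, 467, 700 | 320, 400, 533, 800 |
| 5%, FP | 65, 85, 130, 255 | 63, 84, 126, 253 | 68, 91, 137, 274 |

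The stated counts are those for *reaching* the limits, rounded up.

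**2. False-drop probability for a true 90%/99% test.** FN and FP arise in different participants, so they are independent. No confidence interval enters this calculation.
- 30%, exceed: P(FN ≤ 7) × P(FP ≤ 2) = 0.752 × 0.834 = 0.627, so 37% dropped (38% if the number of cases is random).
- 30%, reach: P(FN ≤ 6) × P(FP ≤ 1) = 0.606 × 0.591 = 0.358, so 64% dropped.
- 5%, exceed: P(FN ≤ 7) × P(FP ≤ 12) = 0.752 × 0.645 = 0.484, so 52% dropped.
- 5%, reach: P(FN ≤ 6) × P(FP ≤ 11) = 0.606 × 0.531 = 0.322, so 68% dropped.

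On false negatives alone, the wording moves the figure from 1 − 0.752 = 25% to 1 − 0.606 = 39%.

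**3. Do the limits follow from 80%/95%?** Exact two-sided 95% lower limits:
- Sensitivity, n = 60: 5 FN 81.6%; 6 FN 79.5%; 7 FN 77.4%.
- Specificity, n = 140: 1 FP 96.1%; 2 FP 94.9%.
- Specificity, n = 1140: 42 FP 95.05%; 43 FP 94.95%.

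Under the planned interval, the largest compatible counts are 5 FN and 1 FP at 30% prevalence, and 5 FN and 42 FP at 5%. An observed sensitivity of exactly 90% (6 FN) falls short of 80%. At 5% prevalence, a test with 12 FP has an observed specificity of 1128/1140 = 98.9%, far above 95%.

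| Interval, 30% prevalence | Largest FN, FP | P(meets both) for a 90%/99% test |
|---|---|---|
| Exact, Wilson or Agresti–Coull, two-sided 95% | 5, 1 | 0.437 × 0.591 = 26% |
| Jeffreys; exact or Wilson one-sided 95% | 6, 2 | 0.606 × 0.834 = 51% |
| Wald, one- or two-sided | 7, 3 | 0.752 × 0.947 = 71% |

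No row gives 7 and 2 together, and none reaches 80%. With 1200 participants at 5% prevalence, the specificity condition is met almost surely, and the exact-interval probability is 44%, set by sensitivity alone.

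**4. Point-estimate reading.** If only the observed values had to reach 80% and 95%, the limits would be 12 of 60 and 7 of 140, and a 90%/99% test would pass with probability 99.4%. The stated limits do not follow from that reading either: 8 FN is an observed sensitivity of 86.7%, and 3 FP a specificity of 97.9%.

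**The case against.** The article does not define meeting a threshold. The section on summary statistics says how estimates will be reported and sets no pass mark, and the criterion may be in the full protocol or the SAP. This stands: 26% is conditional on one reading and should not be quoted without its 26% to 71% range.

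The sample size itself can be recovered at 50% power, so it looks like an undisclosed low-power choice more than a failed sum. This also stands, and the point does not rest on 200 being a miscalculation.

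The limits do screen out poor tests. A test with true sensitivity of 80% has at most seven false negatives in 60 with probability 6.7%; one with true specificity of 95% has at most two false positives in 140 with probability 2.7%. That serves the stated purpose, but the price paid in good tests is left unstated.

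The thresholds are introduced as an example, the 30% scenario only permits dropping, the first evaluations run without stopping criteria, and the figures are to be reviewed. Table 5 separately gives precision-based sizes, including 480 for 90% sensitivity at 30% prevalence. All this lowers the immediate consequence. However, the reason given for the review is how quickly composite-reference information becomes available, not whether the limits are right, and the discussion promotes the rules as a strength.

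A reader might infer that over a third of good tests will in fact be discarded, or reported as below specification. The documents do not support this. The criteria are not yet in force, and nothing says a test is reported as failing because its interval crosses a threshold.

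**Conclusion.** The point holds for the limits as described. They are not the maximum counts compatible with 80%/95%, under the planned exact interval or any other standard interval tried. At 5% prevalence the false-positive limit is 12, where an exact 95% bound would tolerate 42.

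The firmest figures are the false-drop probabilities for a true 90%/99% test: 37% or 64% in the 30% scenario, and 52% or 68% in the 5% scenario, according to whether the limit must be exceeded or reached. They assume the stated accuracy and prevalence, full recruitment, and 60 positives with 140 or 1140 negatives. The higher figure in each pair matches the article's own participant counts.

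The 26% chance of meeting both thresholds with 200 participants rests on the further assumption that the exact two-sided lower limit must reach each threshold.

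A reader might also infer that the study must be enlarged, or that 5 FN and 1 FP should replace the stated limits. Neither follows. The article claims no power. And 5 and 1 describe success at the end of the evaluation; used as limits not to be exceeded, they would drop 1 − 0.258 = 74% of 90%/99% tests.

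**What to change.** Before the stopping criteria are activated:

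1. Define meeting a threshold: interval method, level and sidedness.
2. Restate the probability that a 90%/99% test meets both thresholds with 200 participants at 30% prevalence and 1200 at 5%. Under the exact two-sided 95% interval these are about 26% and 44%.
3. Re-derive the limits from 80%/95%, or stop describing them as the maximum compatible counts and present them as a screening rule.
4. State the false-drop probability of each limit, and of both together, for a 90%/99% test.
5. Use one wording, either reaching or exceeding the limit, in both scenarios and in the participant counts.
6. Express limits per number of reference-positives and reference-negatives, since prevalence will vary.
7. If 5 FN and 1 FP are quoted, label them as the end-of-evaluation criterion under exact intervals, and do not adopt them as stopping limits without stating the 74%.

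The cost is a revised paragraph, one changed sentence in the discussion and a short calculation. No participants are added by correcting the statement, though the stated probabilities become less favourable. For information, at 30% prevalence about 380 participants would give an 82% chance of meeting both thresholds under the exact interval.

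### The futility limit is worded as a count to be exceeded at 30% prevalence and as a count to be reached at 5%, and the printed recruitment counts fit only the second reading

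*Protocol article*

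**What the plan says.** The protocol article gives the rule in three places.

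- **Methods, Stopping criteria, 30% prevalence.** The setting is "Assuming a test with 90% sensitivity, a 99% specificity, and a pre-test probability (prevalence) of 30%, we would require 200 participants". The rule is that "tests with more than seven false negatives or two false positives could be immediately dropped from the study". Read plainly, a test is dropped at its 8th FN or 3rd FP.
- **Methods, Stopping criteria, 5% prevalence.** Here the required N is 1200. The rule reads: "interim futility analyses will stop the evaluation after seven false negatives or twelve false positives". The natural reading is the 7th FN or 12th FP.
- **Discussion, Strengths and limitations.** The criteria are said to pick out "POCTs that have already exceeded the maximum number of false positives or false negatives", which agrees with the 30% wording.

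The Stopping criteria section also prints how many participants are needed before a poor test is identified. At 30% prevalence the rule would "exclude tests with sensitivities of 50%, 60%, 70%, or 80% after the first 50, 60, 80, and 120 participants recruited". The matching counts for specificities of 80%, 85%, 90% and 95% are 15, 20, 30 and 60. At 5% prevalence the printed counts are 280, 350, 470 and 700 for the same sensitivities, and 65, 85, 130 and 255 for the same specificities.

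The section closes by calling these figures indicative, to be reviewed later, and says that the first tests will be evaluated with no stopping criteria in force.

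**The concern.** A stopping boundary has to say whether the stated count triggers the stop or is the last count allowed. Here the two scenarios use the same FN number, seven, and have the same expected number of reference-positives (200 × 0.30 = 1200 × 0.05 = 60), yet the wording puts the stop at different counts. The recruitment counts for the 30% scenario also appear to rest on a different boundary from the one stated just before them.

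One error matters because the limits lie close to what a good test is expected to produce. At 90% sensitivity and 99% specificity the expected counts are 60 × 0.10 = 6 FN, and 140 × 0.01 = 1.4 FP (30% prevalence) or 1140 × 0.01 = 11.4 FP (5% prevalence). A test with 7 FN and 2 FP among 200 participants would be kept under one reading and dropped under the other.

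**Working it through.** **Inputs, all from the Stopping criteria section.** Sensitivity 90%, specificity 99%. At 30% prevalence, N = 200, giving 60 reference-positives and 140 reference-negatives. At 5% prevalence, N = 1200, giving 60 and 1140. Limits are 7 FN and 2 FP at 30%, and 7 FN and 12 FP at 5%.

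**Step 1: reproduce the printed recruitment counts.** The expected recruitment to the k-th error is k / [prevalence × (1 − sensitivity)] for FN and k / [(1 − prevalence) × (1 − specificity)] for FP. For example, at 30% prevalence and 50% sensitivity, 7 / (0.30 × 0.50) = 46.7 and 8 / (0.30 × 0.50) = 53.3.

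| Scenario | Printed | Limit reached (k = limit) | Limit exceeded (k = limit + 1) |
|---|---|---|---|
| 30%, sensitivity 50/60/70/80% | 50/60/80/120 | 46.7/58.3/77.8/116.7 | 53.3/66.7/88.9/133.3 |
| 30%, specificity 80/85/90/95% | 15/20/30/60 | 14.3/19.0/28.6/57.1 | 21.4/28.6/42.9/85.7 |
| 5%, sensitivity 50/60/70/80% | 280/350/470/700 | 280/350/466.7/700 | 320/400/533.3/800 |
| 5%, specificity 80/85/90/95% | 65/85/130/255 | 63.2/84.2/126.3/252.6 | 68.4/91.2/136.8/273.7 |

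Rounded up to the next 10 (sensitivity) or 5 (specificity), the *reached* column gives every printed figure. The *exceeded* column lies above the printed figure in every cell. So the 5% counts agree with their own sentence, and the 30% counts contradict theirs.

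**Step 2: chance that the assumed 90%/99% test is dropped by full recruitment.** Error counts only grow, so the chance of ever crossing a limit is the chance that the final count crosses it. Exact binomial tails:

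- FN ~ Bin(60, 0.10): P(≥7) = 0.394, P(≥8) = 0.248.
- FP ~ Bin(140, 0.01): P(≥2) = 0.409, P(≥3) = 0.166.
- FP ~ Bin(1140, 0.01): P(≥12) = 0.469, P(≥13) = 0.355.

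Either limit is crossed with probability 1 − (1 − P_FN)(1 − P_FP).

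| Scenario | FN trigger | FP trigger | Chance of being dropped |
|---|---|---|---|
| 30%, both exceeded | 8 | 3 | 1 − 0.752 × 0.834 = 37% |
| 30%, only FN limit moved | 7 | 3 | 1 − 0.606 × 0.834 = 49% |
| 30%, only FP limit moved | 8 | 2 | 1 − 0.752 × 0.591 = 56% |
| 30%, both reached | 7 | 2 | 1 − 0.606 × 0.591 = 64% |
| 5%, both exceeded | 8 | 13 | 1 − 0.752 × 0.645 = 52% |
| 5%, both reached | 7 | 12 | 1 − 0.606 × 0.531 = 68% |

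If the number of reference-positives is allowed to vary at random, the four end points become 37.9% and 64.4% (30% prevalence), and 52.1% and 67.9% (5% prevalence).

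**The case against.** The strongest reply is that this text is not yet in force. The figures are called indicative and are to be reviewed, the first tests run without stopping criteria, the 30% sentence is permissive, each new test needs its own protocol amendment, and full statistical detail is left to the SAP. All of that stands. A reader might infer that two teams would already reach opposite decisions on the same data; the document does not support that. It does not remove the contradiction either, because the planned review needs one defined boundary to start from.

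A second reply is that stopping after seven is loose English and could mean once seven have been used up. The wording allows it, but on that reading the printed counts in both scenarios disagree with the rule.

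A third is that the purpose given in the Discussion, finding tests that can no longer reach the target, settles the matter. For FN, a Wald interval supports exceeding: 7 errors in 60 give a lower 95% limit of 80.2% and 8 give 78.1%, against the 80% minimum. But the exact lower limit at 7 errors is already 77.4%. For FP at 30% prevalence against the 95% minimum, the Wald limit is still 95.5% at 3 errors in 140, while the exact limit is 94.9% at 2. The cue depends on the interval and does not give one answer.

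Two further readings are tempting and go too far. The Discussion is not a third rule; it agrees with the 30% sentence, so there are two boundaries. Nor does the FN discrepancy alone move the drop probability from 37% to 64%: it moves it to 49%, and 64% needs both limits to shift by one.

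**Conclusion.** The point holds. The Stopping criteria section sets the boundary in two ways, and the recruitment counts for 30% prevalence contradict the rule they illustrate. Reading everything as exceeded conflicts with the printed counts in both scenarios; reading everything as reached conflicts with the 30% sentence and the Discussion.

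The ambiguity is worth up to 27 percentage points in the chance of dropping a 90%/99% test at 30% prevalence (37% to 64%) and 16 points at 5% (52% to 68%). Only these increments belong to this point: harmonising the wording on exceeding the limit would still leave 37% and 52%. The probabilities assume the protocol's own sensitivity, specificity, prevalence and N, errors counted against the reference result as given, and independent FN and FP counts.

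Because the figures are provisional, this should be corrected before the rule is put into use; it does not affect the first evaluations.

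**What to change.** Choose one boundary, *exceeds* or *reaches*, and use it in both sentences of the Stopping criteria section and in Strengths and limitations.

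- **If exceeds:** reword the 5% sentence to match the 30% one and recompute the recruitment counts from limit + 1. At 30% prevalence these are about 53/67/89/133 (sensitivity) and 21/29/43/86 (specificity); at 5%, about 320/400/533/800 and 68/91/137/274.
- **If reaches:** keep the counts, and change the 30% sentence and the Discussion sentence.

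In either case, report the resulting probability of dropping a 90%/99% test: 37% and 52% (30% and 5% prevalence) if exceeds, 64% and 68% if reaches. The cost is a few words and, for the first option, one recalculation that makes early identification of poor tests look somewhat slower. No data collection changes.
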